## Abstract

**Abstract:**

**Introduction:**

Accurate evaluation of respiratory rate and pattern is important in health and disease; however, it can be challenging in children and babies due to small size and poor tolerability of existing monitoring equipment. This protocol outlines a study evaluating the feasibility of collecting respiratory data using a chest-worn accelerometer-based motion sensor in paediatric patients at risk of apnoea, respiratory failure and sudden death.

**Methods and analysis:**

This is an observational feasibility study over a 2-year period. The biosensor is an accelerometer worn on an ECG electrode during standard care at the Royal Hospital for Children, Glasgow. We aim to recruit three groups of patients (75 patients to each group): (1) Children attending for overnight cardiorespiratory polygraphy (0 to ≤16 years), (2) neonatal inpatients (from 30 weeks gestation) and (3) children attending for video telemetry at the epilepsy monitoring unit (0 to ≤16 years). Measurements will include (1) chest and/or abdominal wall motion measured by the worn biosensors; (2) standard clinical monitoring data will be collected to support biosensor data interpretation and (3) acceptability will be measured by a feedback questionnaire completed by patients and their parents/guardians.

**Ethics and dissemination:**

This study protocol was reviewed and approved by Yorkshire and The Humber-Leeds East Research Ethics Committee, approval number 314 696. This study involves human participants; written informed consent and assent, when appropriate, will be obtained from participants (or their parent/legal guardian/next of kin) to participate in the study. The study will be carried out in accordance with the World Medical Association Declaration of Helsinki (1964) standard reporting. Study findings will be reported clearly and transparently with relevant stakeholders including researchers, practitioners and publicly available databases. Results from this study will be presented at national and international conferences and reported in peer-reviewed publications.

**Trial registration number:**

NCT06292299 pre-results stage.

STRENGTHS AND LIMITATIONS OF THIS STUDYThis study involves data collection from paediatric patients wearing a novel biosensor in a tertiary children’s hospital, with a broad eligibility criteria strengthening external validity.The biosensor data can be paired with standard clinical monitoring data to provide a comprehensive ground truth for data interpretation.Children recruited to this study are at risk of apnoea, sudden death and respiratory failure, a population that may benefit from wearable technology, which can identify changes in respiratory metrics.Movement artefact has the potential to impact the visualisation of the respiratory waveform; however, actigraphy as a metric can have value in monitoring the clinical condition.

## Introduction

 Novel wearable technology has the potential to improve the accessibility and tolerability of respiratory monitoring for paediatric and neonatal patients.^1^ This observational study explores the feasibility of combining a wireless wearable device and data science to support respiratory evaluation in different paediatric patient groups. Longitudinal data collection using wearable technology may provide novel insights into pathophysiology of conditions where abnormal respiratory function or mechanics are suspected of contributing to patient morbidity. Continuous respiratory monitoring can allow identification of signatures and trends warning of clinical deterioration or impending apnoea. The COVID-19 pandemic highlighted the value of wearable technology for remote monitoring and automated diagnosis harnessing advances in technology and artificial intelligence.^1^

Sleep disordered breathing (SDB) in children is common, with prevalence estimated to be around 2%–5% and can have implications for a child both in terms of physical health and neurocognitive development.^2^,^9^ Untreated, SDB is associated with increased risk of cardiovascular and metabolic disease, as well as developmental, learning and behavioural issues.^10^,^13^ Gold standard paediatric sleep diagnostics requires complex multichannel tests in specialised centres, limiting access and availability, resulting in delayed diagnosis and management.^14^ Early identification and treatment of SDB has been shown to improve outcomes.^15^ SDB is more prevalent among children with genetic syndromes and neurodevelopmental disorders, who can find gold standard diagnostic evaluation challenging.^16^,^19^ The nasal cannula and thermistor have been identified as most challenging to tolerate, particularly for younger children.^20^ The reliance on diagnostics equipment which is not acceptable to a patient population leads to health disparities.

Evaluating respiratory rate (RR) and pattern in neonatal patients is a crucial part of routine monitoring of the newborn. RR is also an indicator of respiratory distress and apnoea of prematurity which can have neurodevelopmental consequences if not identified and treated appropriately.^21 22^ Respiratory monitoring in neonatal patients can be challenging due to their small size, higher RR and low tidal volume (TV). There is consequently a need for lightweight wireless wearable technology suitable for neonatal patients.^23^,^25^ Similarly, newborn term babies, which are typically unmonitored on postnatal wards, can have an unexpected collapse which, although rare, can have catastrophic outcomes.^26 27^ Controversies exist around home monitoring for sudden unexpected death in infants; however, cardiorespiratory monitoring following a previous brief resolved unexplained event can be considered.^28^

Children with epilepsy are at increased risk of sudden unexpected death in epilepsy (SUDEP), the pathophysiology of which remains unclear; however, recent evidence suggests that terminal events are commonly preceded by central apnoea.^29^,^31^ Improving our understanding of SUDEP is fundamental for prevention and development of an alert system for family members or healthcare providers. The landmark Mortality in Epilepsy Monitoring Unit Study showed that resuscitative efforts were delayed in SUDEP in epilepsy monitoring units.^29^ Resuscitation was initiated within 3 min of cardiorespiratory arrest in non-fatal cases but delayed by at least 10 min in fatal cases. In epilepsy syndromes, such as Dravet’s, 20% of individuals die before 20 years old; 50% of these from SUDEP.^32^,^34^ An alarm and rapid response to children who have apnoea in association with seizures could save lives (1.2/1000 deaths per year in UK).^29 35^

The PneumoWave biosensor is a small device (40 mm in diameter and 14 mm in height, 20 g in weight) that attaches onto the chest/abdomen using an ECG electrode and is intended to capture and store chest motion data continuously over a period shown in figure 1. The device will be used in a research application to assess activity where quantifiable analysis of physical motion is desirable and has the potential to be used to detect changes in breathing patterns, as well as detect reduced chest movement and cessation of breathing. During this study, we aim to determine the feasibility of collecting respiratory waveform data from three groups of paediatric patients at risk of apnoea, where accurate monitoring of RR and pattern can be challenging.

**Figure 1 F1:**
[figure not shown]
PneumoWave biosensor and placement on the body. (A) Image of biosensor. (**B**) Location of biosensor placement for attending for evaluation of sleep disordered breathing will wear a chest and abdominal biosensor to allow for evaluation of paradoxical thoracoabdominal excursions (paradoxical breathing). (C) Location of biosensor placement for neonatal patient. Patients with epilepsy attending for video telemetry will wear a chest biosensor.

This study aims to (1) determine the feasibility of collecting respiratory data from wearable accelerometer-based biosensor in children attending for cardiorespiratory polygraphy (CR-P) sleep studies, neonatal patients and children with epilepsy attending for video telemetry (VT), (2) interrogate biosensor data in line with standard clinical monitoring to assess potential for RR, pattern and apnoeas, (3) explore patients’ and parents’ acceptability of the wearable biosensor, (4) identify novel clinical pathway candidates which include accelerometry to address unmet needs in paediatric diagnostics and longitudinal clinical monitoring and (5) capture longitudinal data from children with conditions associated with unexpected collapse to identify digital biomarker candidates for future research.

## Methods and analysis

### Study design

This is an observational diagnostic feasibility study over a 2-year period aiming to collect biosensor data from 75 patients in each of the three groups: CR-P (sleep study), neonates and VT (epilepsy). Patients who consent to take part will be assigned a study number which will be linked to demographic information as well as standard clinical monitoring data.

### Eligibility criteria

#### Inclusion criteria

Patients in the CR-P group must be (1) undergoing CR-P, (2) ≤16 years old and (3) patients and/or parents/guardians must speak and read English. Patients in the epilepsy group patients must be (1) attending for VT, (2) ≤16 years old and (3) patients and/or parents/guardians must speak and read English. Patients in the neonatal group must be (1) staying in the neonatal unit or postnatal wards, (2) ≥30 weeks’ gestation and (3) parents/guardians who speak and read English.

#### Exclusion criteria

Exclusion criteria for all three groups include (1) outside age range, >16 years of age for CR-P/VT patients or <30 weeks corrected gestation for neonatal patients, (2) broken skin over chest/abdominal area, (3) sensitivity to ECG electrodes, (4) implanted pacemaker device in situ and (5) in the clinical opinion of the investigator, the patient is not suitable for inclusion.

### Objectives

The primary objective of the study is to assess the feasibility of collecting respiratory waveform data using the PneumoWave biosensor in children attending for CR-P, neonatal inpatients on a range of respiratory support, including those unsupported and patients with epilepsy attending for VT. The secondary objective is to view biosensor respiratory waveform alongside standard clinical monitoring data. We will collect data on biosensor acceptability from the patient (as able) and parent/guardian.

### Outcome measures

#### Primary outcome measures

Feasibility of collecting respiratory waveform data using PneumoWave biosensor in paediatric patients attending for CR-P, VT and neonatal patients. (1) We will quantify the length of time the device is on each patient compared with monitoring time, (2) if the device is removed by the patient/other and (3) the ability of the device to collect data while in situ.

#### Secondary outcome measures

Secondary outcomes include collating respiratory data from standard clinical monitoring and viewing biosensor data to evaluate potential for PneumoWave to evaluate normal and abnormal RR/pattern. Standard clinical monitoring data will be used to provide a ‘ground truth’ to support algorithm development and refinement. Examples of standard clinical data include RR count by clinical team, respiratory inductance plethysmography (RIP) band waveform data from CR-P, ventilator measured parameters including RR and TV, apnoeas scored by physiologists from CR-P. We will observe different types of respiratory events, including obstructive and central apnoea and hypopnoea, as well as respiratory pattern changes, including periodic breathing and hypoventilation reflected in elevated transcutaneous carbon dioxide (TcCO_2_).

#### Acceptability

We will assess the acceptability of the biosensor by providing feedback questionnaires to patients and parents at the end of the monitoring period. Feedback forms have been developed for children 6–11 years of age and 12–16 years of age.

### Data collection process and study timeline

Patients will be identified by the usual care team and consented for participation, as shown in figure 2 and table 1. Families expressing interest in the study will be approached by a member of the research team who answered any questions, and written informed consent/assent will be obtained when appropriate, as shown in figure 2 and table 1.

**Figure 2 F2:**
[figure not shown]
On-site workflow for observational study. Group 1 includes children attending for cardiorespiratory polygraphy; group 2 includes neonates staying in the neonatal unit or postnatal ward and group 3 includes children attending the epilepsy monitoring unit for video telemetry. Green boxes represent ethics forms. CR-P, cardiorespiratory polygraphy; DCM, data capture mobile; PEWS, Paediatric Early Warning Score; PIS, participant information sheet; VT, video telemetry.

**Table 1 T1:** Data sources

Patient group	PneumoWave sensors worn	Standard clinical monitoring data	Outcome of interest
Cardiorespiratory sleep study patients	Chest and abdominal sensor	Thoracic and abdominal RIP channels, RIP sum, Oximetry (SpO_2_ and HR), ECG, body position, movement and nasal pressure flow (all children), video, audio and TcCO_2_ (some children)	Tolerability of PneumoWave device Feasibility of data collection from PneumoWave device RR Apnoeas and hypopnoeas (obstructive, central, mixed)
Neonatal patients	Chest sensor	Oximetry (SpO_2_ and HR)	Tolerability of PneumoWave device Feasibility of data collection from PneumoWave device RR Central apnoeas/periodic breathing
Epilepsy patients attending for video telemetry	Chest sensor	Oximetry (SpO_2_ and HR) Video EEG Feedback forms completed by parents and children >5 years of age	Tolerability of PneumoWave device Feasibility of data collection from PneumoWave device RR Central apnoeas in peri-ictal period Respiratory pattern in peri-ictal period Parent/patient feedback on biosensor acceptability

EEG, electroencephalogram; HR, heart rate; RIP, respiratory inductance plethysmography; RR, respiratory rate; SpO_2_, peripheral oxygen saturation; TcCO_2_, transcutaneous carbon dioxide.

### Data collection from patient groups

Patients attending for CR-P will wear a chest and abdominal biosensor shown in figure 3 and tables1  2. CR-P is recorded using SOMNOscreen (SOMNOmedics, Germany). Respiratory effort is measured using thoracic and abdominal RIP bands, alongside the derived RIP sum channel for surrogate flow analysis if required. Oxygen saturation (SpO_2_) and pulse rate are measured by Nonin integrated probe. ECG, body position, movement and nasal pressure flow are routinely recorded, while video, audio and TcCO_2_ are recorded in some children. CR-P recordings will be scored by sleep physiologists according to American Academy of Sleep Medicine (AASM) guidelines used to diagnose SDB, allowing identification of different types of apnoeas and hypopneas (obstructive, central, mixed), breathing patterns including periodic breathing and hypoventilation.^36^

**Figure 3 F3:**
[figure not shown]
Data collection using novel biosensors in CR-P patients. Children attending for CR-P will wear a chest and abdominal biosensor attached using ECG electrodes. Biosensors are positioned in the midline next to RIP bands. CR-P equipment will be worn as per standard clinical practice. Accelerometer data are transferred via Bluetooth from each biosensor to an application on a mobile device. Data are then stored in a cloud. Data downloaded from the cloud (x, y, z axis) are processed, smoothed, zero meaned and combined to generate a respiratory waveform. CR-P, cardiorespiratory polygraphy; CO_2_, carbon dioxide; HR, heart rate; RIP, respiratory inductance plethysmography; RR, respiratory rate; SpO_2_, peripheral oxygen saturation.

**Table 2 T2:** Summary of study procedures

Study procedure	Screening/consent (first visit)	Research episode	28 days follow-up electronically
Obtain informed consent where relevant	√		
Review inclusion/exclusion criteria	√		
Complete case report form*	√	√	√
Collect continuous data from standard care vital sign monitor		√	
Collect waveform respiratory data		√	
Review retrospective notes for adverse outcome			√

* Demographics (gender, age, ethnicity), medical history, sleep history, medication history, date/time of monitoring period, position of sensor on body and position patient (supine, prone, right/left lateral) and concurrent activities (eg, feeding, nappy changing, being held by parents), adverse event monitoring, patient and parent satisfaction form.

The PneumoWave data capture mobile (DCM) system consists of a wearable biosensor and a data collecting app running on an Android mobile platform and a cloud storage and viewing dashboard. Accelerometer data can also be downloaded from the portal for analysis. Acceleration data will be transferred to a secure cloud for storage and data analysis.

Patients in the neonatal unit will wear a single chest sensor in addition to standard clinical monitoring for a period of 1–6 hours (table 1). Neonates in the postnatal wards are largely unmonitored and therefore a Masimo Radical 97 will be used to collect concurrent SpO_2_ (oxygen saturation), heart rate and RRp (respiratory rate derived from plethysmography waveform) data. Patients in the special care baby unit who may be receiving respiratory support (including oxygen therapy, high flow oxygen therapy or non-invasive positive airway pressure) will have continuous oximetry monitoring. Neonates in intensive care may be receiving invasive mechanical ventilation of different modes supporting patient-triggered breaths (patient-triggered ventilation, synchronised intermittent mandatory ventilation) to mandatory breaths. Ventilator measured parameters including RR, TV as well as inspiratory time as well as inspiratory time, peak inspiratory pressure and positive end expiratory pressure will be recorded.

Patient attending for VT assessment will wear a single chest biosensor in addition to electroencephalogram (EEG) (Natus, Neuroworks software) video and Masimo Radical-97 or Masimo Radical-7 touch oximetry monitoring for the duration of their stay (1–4 days) (table 1).

During the monitoring period, case report forms (CRFs) will be completed as shown in table 2. CRFs were designed to capture data on participant demographics, medical history, current medication, information related to biosensor monitoring including time/duration of monitoring, position of biosensor on patient, patient position (supine, prone, right or left lateral), events or patient activities during monitoring (eg, breastfeeding, held by parents), and whether monitoring was tolerated by the participant.

### Sample size

This is a feasibility study to generate data for future prospective interventional studies. A total of 225 patients will be recruited with an aim of 75 patients from each study group. 75 patients per group was decided to be an appropriate number to provide a range of apnoea types, range of comorbidities, demographics and to evaluate tolerability across a diverse patients group representative of patient population to support external validity.

### Statistical analysis

Data was stored in Microsoft Excel and analysed using PRISM 10 (San Diego, California, USA). Demographic data, feedback forms and descriptive data will be reported using means and SD for continuous data. Absolute number and percentages will be reported for categorical data. Any statistical software can be used. For reference events (eg, apnoeas) or respiratory metrics (eg, RR), Root Mean Square Deviation to quantify the accuracy of manually annotated biosensor data (and developmental algorithm results) compared with standard care. A target accuracy of ±2 bpm/% of RR will be predefined as clinically acceptable error margin. Bland-Altman analysis will additionally be performed to visualise the bias between measurements. For respiratory event identification (eg, central apnoea), a confusion matrix stating the true positive (TP), false positive (FP) and false negative (FN) values of biosensor data (and developmental algorithm detection) of a specific respiratory event will be generated. Receiver operating characteristic curve analysis will be undertaken to evaluate the predictive performance of algorithms for evaluating central apnoeas in CR-P patients.

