### Biosensor analysis

Biosensors data will be interpreted blinded to CR-P data scored by physiologists according to AASM guidelines to evaluate potential for apnoea detection and interrogation of RR and pattern using RIP bands as ground truth. TcCO_2_ data provide an indicator of hypoventilation.

For neonatal patients, biosensor data will be paired with oximetry data and viewed alongside SpO_2_ trace, recorded RR observation and ventilator measured parameters when available.

For patients with epilepsy, biosensor data will be interpreted in the context of VT, EEG evidence of epileptic seizures and video recording for breathing effort in the peri-ictal period.

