### Algorithm under test

Developmental versions of central apnoea algorithm/actigraphy algorithm, RR algorithm.

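### Algorithm accuracy is to be assessed on the same study's reference data that serve to develop the algorithms, with no stated version lock or patient-level separation, so it may be apparent rather than predictive performance

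*Protocol article*

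**What the plan says.** Four places in the protocol article bear on this.

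- **Secondary outcome measures** gives the standard clinical monitoring data the role of ground truth, and the stated purpose is "to support algorithm development and refinement".
- **Algorithm under test** lists what is evaluated: "Developmental versions of central apnoea algorithm/actigraphy algorithm, RR algorithm".
- **Statistical analysis** uses "Root Mean Square Deviation to quantify the accuracy of manually annotated biosensor data (and developmental algorithm results) compared with standard care". It adds a confusion matrix giving the true positive, false positive and false negative "values of biosensor data (and developmental algorithm detection) of a specific respiratory event will be generated". For central apnoea it adds: "Receiver operating characteristic curve analysis will be undertaken to evaluate the predictive performance of algorithms for evaluating central apnoeas in CR-P patients".
- **Sample size** treats the patients as one pool per group: "A total of 225 patients will be recruited with an aim of 75 patients from each study group". No subset is set aside for development or for testing.

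The Biosensor analysis section adds a safeguard for the sleep-study group: "Biosensors data will be interpreted blinded to CR-P data scored by physiologists according to AASM guidelines".

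**The concern.** One set of patients and one reference standard are given two jobs: shaping the algorithms and scoring them. An algorithm adjusted to agree with the scored events of certain children will agree better with those children than with new ones. Reporting that agreement as predictive performance claims more than the data can show.

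Each of the three algorithm summaries is exposed. The ROC curve is inflated if features or weights were chosen on the same children. The confusion matrix is inflated even with a fixed score if the detection threshold is picked on the same children. The RMSD for respiratory rate is compared with an error margin of ±2 that the plan calls clinically acceptable, and meeting that margin on tuning data would not show that it is met in new children.

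The results have a further use. The Sample size section says: "This is a feasibility study to generate data for future prospective interventional studies". The Discussion foresees non-inferiority studies of the algorithms, so an inflated sensitivity or AUC could enter their planning assumptions.

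**Working it through.** **The plan's own figure.** 3 groups × 75 patients = 225, which reproduces the stated total. The article gives no target AUC or sensitivity, expected number of apnoeas, number of algorithm parameters or split size. The size of any optimism therefore cannot be derived from its own inputs.

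**The passages side by side.**

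1. Development and refinement use this study's reference data (Secondary outcome measures).
2. Accuracy is measured against this study's reference data (Statistical analysis).
3. What is measured includes developmental versions (Algorithm under test, Statistical analysis).
4. No passage says that a version is frozen before step 2, or that steps 1 and 2 use different patients.

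For any algorithm tuned under step 1 and scored under step 2 on the same children, the estimate is apparent performance. Its expected bias is upward:

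optimism = (mean AUC on the patients used for fitting) − (mean AUC of the same fitted rule in new patients).

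**Illustration of size.** Every input below is an assumption except the 75 patients. Each simulation has one truly informative feature, with the rest noise.

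*Simulation A:* 75 children × 100 epochs, mean event rate about 2% varying by child (about 75 × 100 × 0.02 = 150 events), child-level noise, logistic model, 40 replicates.

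| Candidate features | Apparent AUC | AUC in new children | Optimism |
|---|---|---|---|
| 10 | 0.727 | 0.665 | 0.062 |
| 20 | 0.746 | 0.641 | 0.105 |
| 40 | 0.788 | 0.633 | 0.155 |

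*Simulation B:* 75 patients × 40 windows, 5% with an event (about 75 × 40 × 0.05 = 150 events), informative feature shifted by 1 SD, linear score, between-patient variance share 0 or 0.3, 60 replicates.

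| Features | Optimism, share 0 | Optimism, share 0.3 |
|---|---|---|
| 2 | 0.763 − 0.761 = 0.002 | 0.749 − 0.745 = 0.004 |
| 10 | 0.769 − 0.756 = 0.013 | 0.762 vs 0.734: 0.029 (from unrounded means) |
| 20 | 0.774 − 0.744 = 0.030 | 0.769 − 0.723 = 0.046 |
| 40 | 0.785 − 0.732 = 0.053 | 0.797 − 0.703 = 0.094 |

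**A locked rule.** In simulation B the informative feature alone, with nothing fitted, was scored on the same 75 patients. With share 0 its AUC was 0.756 to 0.762, against a true value of Φ(1/√2) = 0.760. There is no optimism when the rule is fixed beforehand, however many patients are then used to test it.

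**Cost of a hold-out.** 95% half-width for a per-patient proportion of 0.80 = 1.96 × √(0.80 × 0.20 / n):

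- n = 75: 0.091
- n = 50: 0.111
- n = 38: 0.127
- n = 25: 0.157

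**The case against.** The strongest reply is that the article is silent here rather than wrong. Nowhere does it say that an algorithm will be tested on the children used to tune it. Talk of refinement suggests that algorithms already exist, and a version that predates the data and is only tested on them carries no such bias. Splits and version locks are often specified in a full protocol or SAP, and neither is shown. This stands to a degree: overlap is implied, not stated, and its absence from the article does not prove its absence from the study. What remains is that the article itself assigns both uses to the same data and names the result predictive. How folds are built is SAP detail. Whether development and test patients differ decides what the estimate means.

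A second reply is that part of the analysis is immune. This stands in full. Manual annotation of the biosensor trace has no parameters fitted to these patients, and in the sleep-study group the reading is blinded to the physiologists' scoring. A reader might infer that every RMSD and confusion matrix in the plan is inflated, and the document does not support that. The blinding does not, however, stop an algorithm from being refined against the scored events and then tested on them.

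A third reply is that little depends on these results. The primary outcome is wear time, removal and the ability to collect data, and the Discussion leaves algorithm effectiveness to later studies. This also stands, and it limits the weight of the point. A reader might also infer that a later trial will be under-sized, but no passage says that these estimates will set a later sample size.

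**Conclusion.** The point holds in conditional form. The article gives the reference data both roles and states no lock or patient-level separation. Where tuning and testing share patients, the algorithm RMSD, confusion-matrix and ROC results are apparent performance and will be optimistic.

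The direction is firm under that condition, but the size is not. It runs from about 0 for a pre-locked or two-feature rule to roughly 0.1 to 0.15 in AUC with 40 candidate features. The two simulations give 0.094 and 0.155 at that upper end, and the gap between them shows how far the figure depends on assumed event rates, clustering and degree of tuning. It would be tempting to say that the reported performance is bound to be inflated by a stated amount. The document supports neither the certainty nor the figure.

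Severity is moderate: secondary outcomes of a feasibility study are affected, and the primary outcome is not.

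**What to change.** Add to the Statistical analysis and Algorithm under test sections wording such as:

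> *Algorithm performance (RMSD, confusion matrix, ROC) is estimated either with an algorithm version locked before this study's data are used, or by nested cross-validation with whole patients as the unit, including the choice of threshold. Any result obtained on patients used for development is labelled apparent performance.*

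The unit must be the patient, because epochs from one child resemble each other and an epoch-level split would leave the same child on both sides. Cross-validation is valid only if every tuning step can be repeated inside each fold. Refinement by hand needs a lock or a hold-out instead.

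No extra patients are needed. The cost is version control, a little more analysis work and probably a less favourable headline figure. A hold-out of the later-recruited third is possible, but would leave 25 patients per group for evaluation and widen the half-width for a proportion of 0.80 from about 0.09 to 0.16. Cross-validation, or a lock tested on all 75, is therefore preferable where it can be done.
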